## INTERVENTIONS

5

### General training characteristics

5.1

Each training occurred in‐person with no more than 30 participants, lasting 3‐3.5 hours with one or two breaks totaling approximately 30 minutes. Training sessions were interactive in nature (eg, group discussions, case studies) and structured with a Power‐Point presentation with notes and provision of relevant resources. A standardized fidelity checklist was used to document key points covered (or not covered in the control group) during the training.

### Let's talk about pain training

5.2

Previously developed and piloted by [name] and colleagues,^13^ the training's content was specific to children with I/DD and focused broadly on providing information on what pain is, pain expression, pain assessment, and pain management specific to a respite context; detailed training outline is available upon request. *Let's Talk About Pain* is empirically informed and covers all relevant aspects of Chapter 43 of the IASP Core Curriculum for Professional Education in Pain.^16^ The training was facilitated by the same facilitator throughout the study.

### Control training

5.3

Participants in the control group completed a training about a family‐centered care approach. Specifically, the training provided information about the F‐words of childhood disability (function, family, fitness, fun, friends, future; [17]) and how to implement this framework in a respite setting. This translational work is based on the World Health Organization's (2001) International Classification of Functioning, Disability and Health Framework. The topic is fitting given its relevance to care of children in respite settings and its lack of focus on pain. This training was facilitated by a PhD Candidate from McMaster University (Hamilton, ON, Canada).

## OUTCOME MEASURES

6

### Primary

6.1

Participants’ pain‐related knowledge was assessed at pre, post, and follow‐up using the *Questionnaire for Understanding Pain in Individuals with Intellectual Disabilities—Caregiver Version Revised (QUPID‐CR)*, a 39‐item true/false and multiple‐choice questionnaire. Single points are awarded for each correct response to compute a total score out of 39, and higher scores represent greater levels of knowledge. The QUPID‐CR was developed following initial responsivity and item‐level analyses of the original QUPID‐C^18^ completed prior to use in this RCT.^19^ Like the QUPID‐C, the QUPID‐CR is based on existing literature and the International Association for the Study of Pain's (IASP) core curriculum (Chapter 43; [16]).

### Secondary

6.2

Participants provided 6 self‐report ratings (Pain Assessment and Management Perceptions) of their perceptions of (1) the feasibility of (0 = *Not Feasible At All,* 10 = *Highly/Extremely Feasible*), (2) their confidence in (0 = *Not Confident At All*, 10 = *Highly/Extremely Confident*), and (3) their skill in (0 = *Not Skilled At All*, 10 = *Highly/Extremely Skilled*) pain assessment and management for children with I/DD at all three time points. These ratings have shown responsivity to training.^13^, ^18^

Participants also completed a researcher‐developed questionnaire at post, rating their level of agreement (0 = *strongly disagree* to 10 = *strongly agree*) with different statements about the training program (eg, effectiveness of format). Here, participants also provided responses to open‐ended questions related to the training program (eg, what component of the training they thought contributed most to their learning). This questionnaire is based on that which was used in the pilot study for the *Let's Talk About Pain* training.^13^

### Tertiary

6.3

Participants’ use of pain assessment and management skills was assessed using both questionnaire and focus group methodology (see Figure 1). The *Use of Pain Assessment and Management Strategies Questionnaire* is a researcher‐generated questionnaire which includes open and closed questions about the following: (a) participants’ work in a respite setting (eg, number of shifts/hours per week) and (b) frequency of and types of pain assessment and management strategies used. These questions are intended to explore participants’ use of pain assessment and management strategies within the context of their work environment. This questionnaire also contains a previously developed vignette to explore their use of pain assessment and management strategies in a more standardized way.^20^ This vignette has shown divergent and convergent validity when compared to other pain‐related vignettes with different pain sources and background information.^20^

The aim of the focus group component was to explore the types of pain assessment, and management strategies RW have used on the job more in depth. Each began with a brief introduction of the purpose followed by semi‐structured questions about participants’: (1) opinions and knowledge about pain in children with I/DD and (2) experiences with pain assessment and management in respite settings, specifically in the time period between completion of the training and the follow‐up data collection. They were also asked about times when they remembered something from the training and whether they were able or unable to use it; the full focus group guide is available upon request. Audio‐recorded focus groups were 30 minutes to one hour in length, with no more than 12 participants per focus group.^21^ The number of focus groups was dependent on the number of participants attending each organization's follow‐up data collection. Focus groups were facilitated by the lead researcher with an accompanying research assistant taking field notes.^21^

## PARTICIPANT COMPLIANCE AND LOSS TO FOLLOW‐UP

7

Given the single time point nature of the intervention and previous data from the *Let's Talk About Pain* pilot study,^13^ participant compliance was not of great concern. In contrast, the potential to lose participants at the follow‐up time point was more unknown. Incentives were used during the initial data collection (pre, post) and follow‐up to try to maximize participant retention. Specifically, participants received an entry into a $20 gift card draw (odds of winning: 1 in 25) and refreshments at each visit (ie, at the pre/post data collection date, and at follow‐up), a notebook and pen set at the initial time point, and a certificate along with a $20 honorarium at follow‐up.

## ANALYSES

8

Research assistants double enter the data into an SPSS statistical analysis program which is stored on an encrypted, password protected e‐drive. Hard copy data will be stored for seven years after publication of results.

Both intention‐to‐treat (ITT) and per protocol (PP) analysis approaches will be used to analyze the data related to the study's primary and secondary outcomes regarding participants’ pain knowledge and pain assessment and management perceptions; ITT will be primary, and PP will be complementary.^22^, ^23^ After confirming there are no baseline differences between groups, seven 2 × 3 mixed analysis of variances (ANOVA) will be conducted. If statistical assumptions for these analyses are not met, a more conservative approach using bootstrapping will be considered and conducted if the program allows; SPPS has some limitations in this regard.^24^ The dependent variables for the different mixed ANOVAs will be the mean of participants’ pain‐related knowledge (primary outcome measure) and pain assessment and management perception rating scores (secondary outcome measures). In all seven analyses, the within‐subjects factor will be represented by participants’ scores on the related measure across pre, post, and follow‐up time periods, and the between‐subjects factor will be the condition (pain training or control training). In keeping with the study's specific hypotheses, follow‐up analyses using one‐way ANOVAs and paired samples *t* tests will be used as needed to further investigate differences in the dependent variables over time within the pain training group if significant group differences are found.

Frequency and descriptive analyses will be used to analyze participant open‐ended responses on the *Use of Pain Assessment and Management Strategies* and training evaluation questionnaire. To describe responses to open‐ended questions, coding schemes will be developed from an essentialist/realist perspective using an unconstrained matrix.^25^, ^26^ In this scheme, both inductive (ie, consideration of participant responses) and deductive (ie, consideration of relevant research literature) approaches will be incorporated as relevant. For example, category names and descriptions will reflect what is known from previous literature as relevant, but new categories will also be developed that may not be consistent with the literature should they arise. First, the primary investigator will become familiarized with the data, and initial categories will be generated and grouped into broader categories with definitions.^27^ These schemes will then be reviewed by additional researchers on the team who will: (a) help to ensure that the schemes are representative of the data and (b) further develop category definitions and examples.^27^ Following coding scheme development, two research assistants will be trained on these schemes. Participant responses will then be coded, and inter‐rater reliability for coding will be calculated using Cohen's Kappa. An inductive and essentialist/realist qualitative thematic analysis following the steps outlined by Braun and Clarke^28^ will be used to analyze focus group transcript data. Following familiarization with the data, transcriptions will be uploaded to NVivo12 software where meta‐ and subthemes will be derived, defined, and refined. How often a topic is raised, the length of time it is discussed, existing research literature, and applied researcher experience in the field will all be considered in developing these themes. Analyses will occur at the semantic level. Intervention and control focus groups will be analyzed separately from one another.

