### Sample size

4.5

G*Power 3^15^ was used to conduct a power analysis based on our previous *Let's Talk About Pain* training pilot study.^13^ Based on the smallest effect size (*d* = 0.90 [effect size *f* = 0.45]; original range of effect sizes *d* = 0.90‐1.71), a very small sample size (16) was required at power of 0.95 and alpha of 0.05 to detect an overall interaction effect of group by time. A much more conservative effect size (*d* = 0.25 [effect size *f* = 0.1250]) was also used to calculate the most stringent estimate at power of 0.95 and alpha of 0.05, resulting in a total target sample size of approximately 84 participants per group (168 participants total; [15). We aimed for our study sample size to fall in the higher end of this range.

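### Intention-to-treat is primary, but the only model named is a three-time-point mixed ANOVA, which keeps only workers with all three scores unless missing ones are imputed

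*Protocol article*

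**What the plan says.** The Analyses section applies two approaches to knowledge (primary outcome) and the perception ratings (secondary): "ITT will be primary, and PP will be complementary". It then fixes the model: "seven 2 × 3 mixed analysis of variances (ANOVA) will be conducted". In all seven, the within-subjects factor is "represented by participants’ scores on the related measure across pre, post, and" follow-up, and the between-subjects factor is the training received. The data are held in SPSS. Bootstrapping is the only fallback, reserved for failed statistical assumptions. One-way ANOVAs and paired t tests may follow within the pain training group if the groups differ.

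The section on compliance and loss to follow-up has little worry about compliance, because the intervention is a single session. It treats attrition differently: "In contrast, the potential to lose participants" at follow-up is described as less well known, and incentives are listed to limit it. No loss rate is given. The Sample size section gives 168 participants in total for f = 0.125 and 16 for f = 0.45, both at power 0.95 and alpha 0.05, with no stated allowance for loss.

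**The concern.** A mixed ANOVA in its usual form needs a complete set of repeated scores from each person. Pre and post are collected around one training session, while follow-up is a separate in-person visit 4 to 6 weeks later, so most missing scores should fall at follow-up. Without imputation, a worker who attends the training and completes pre and post but misses follow-up contributes nothing to the group-by-time test. The immediate post scores are lost as well, although the hypotheses section predicts a group difference at that time.

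Two things are at stake. The first is the population: an analysis labelled ITT would in practice cover those who came back. The second is the estimate: if the workers who do not return differ in score from those who do, and this loss is not the same in the two arms, the completer contrast is biased.

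**Working it through.** **1. The texts side by side.** ITT requires that consented workers be analysed in the arm to which their organization was randomized. The named model requires three scores per worker. The two agree only if nobody misses a time point or a further step supplies the missing scores. The article foresees loss and names no such step. Bootstrapping does not restore missing observations.

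**2. Reproducing the plan's sample sizes.** From the article: two groups (k = 2), three times (m = 3), alpha 0.05, f = 0.125 or 0.45. Assumed, because not stated: correlation ρ = 0.5 between time points and sphericity (ε = 1). For the interaction,

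λ = f² · N · m / (1 − ρ), df1 = (k − 1)(m − 1) = 2, df2 = (N − k)(m − 1).

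- f = 0.125, N = 168: λ = 0.015625 × 168 × 3 / 0.5 = 15.75, df2 = 332, critical F = 3.02, power 0.952. N = 166 gives 0.950 when rounded but lies just below the target (0.9497), so 168 is the smallest even N.
- f = 0.45, N = 16: λ = 0.2025 × 16 × 3 / 0.5 = 19.44, df2 = 28, power 0.970.

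Both stated figures are reproduced. The calculation takes every counted participant to have all three scores.

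**3. Completers only.** Loss rates are assumptions. The number of completers is rounded to an even total.

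| Loss | Completers | Workers discarded | λ at f = 0.125 | Power at f = 0.125 | Power at f = 0.45 |
|---|---|---|---|---|---|
| 0% | 168 | 0 | 15.75 | 0.952 | about 1 |
| 20% | 134 | 34 | 12.56 | 0.894 | about 1 |
| 30% | 118 | 50 | 11.06 | 0.850 | about 1 |

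**4. What an all-available-data model regains.** Same assumptions, with pre and post scores kept for workers missing follow-up, and the effect scaled so that power is 0.952 with no loss.

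| Effect pattern | Power at 20% loss | Power at 30% loss |
|---|---|---|
| Completers only, either pattern | 0.894 | 0.850 |
| All data, effect at follow-up only | 0.902 | 0.863 |
| All data, post effect maintained | 0.942 | 0.937 |

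Little is regained under the first pattern and most of the loss under the second, which is the one the hypotheses predict.

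**5. Bias.** A simulation took a true follow-up difference of 0.25 SD, with the chance of loss rising as the worker's own follow-up score falls (logit slope 0, 0.5 or 1 per SD). All of these values are assumed.

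| Loss, control / pain training | Slope 0 | Slope 0.5 | Slope 1 |
|---|---|---|---|
| 20% / 20% | 0.25 | 0.25 | 0.25 |
| 20% / 40% | 0.25 | 0.34 | 0.41 |
| 40% / 20% | 0.25 | 0.15 | 0.09 |

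Loss that differs by arm but is unrelated to score (slope 0) leaves the contrast unbiased. So does score-related loss of equal extent in both arms. Bias appears when loss is related to score and also differs between arms.

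**The case against.** The strongest reply is that deletion is nowhere in the plan. It is the default behaviour of the model on unimputed data, and imputing before the ANOVA would be consistent with every sentence of the Analyses section. Naming ITT and PP separately suggests that the two sets were meant to differ. Missing-data handling and definitions of analysis sets are also commonly left to a full protocol or SAP, which is not at hand. This stands to a point: an unstated policy is not by itself an error, and the article cannot be said to prescribe deletion. The remaining problem is in what the article does fix, namely ITT as primary together with a model that needs complete data, when loss is expected.

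Three further limits stand. The planned paired t tests from pre to post need only those two scores, so workers lost later can remain in them; the loss of observed data concerns the omnibus test. Nothing in the article indicates that loss was related to score or differed between arms. The power figures use the deliberately stringent effect size, and at the smallest pilot effect the loss of power is negligible.

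**Conclusion.** The point holds in a limited form: the stated method does not secure the ITT label. Unless scores are imputed first, the omnibus group-by-time test would be a completer analysis.

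A reader might go further and infer that the plan orders incomplete cases to be dropped, that the ITT result is therefore certain to be a completer result, and that the PP analysis adds nothing. The article does not support this. It states no deletion rule, does not exclude imputation, and defines neither set. A reader might also infer that any difference in attendance between arms biases the result; the simulation shows that arm-dependent loss alone does not.

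The size is conditional. At f = 0.125, power falls from 0.952 to 0.894 with 20% loss or 0.850 with 30%, given correlation 0.5, sphericity and no allowance for clustering by organization. At f = 0.45 it stays near 1. Bias could be negligible or substantial, depending on a loss mechanism that the article cannot reveal.

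**What to change.** For the primary ITT analysis, fit a linear mixed model for repeated measures to all available scores of every consented worker, with group, time and their interaction, by the arm to which the organization was randomized. Multiple imputation before the planned ANOVA would also serve, if stated. Keep the completer ANOVA as a sensitivity or PP analysis.

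The cost is a change of SPSS procedure (MIXED in place of the repeated-measures general linear model). The Trial status section reports data collection complete and analyses ongoing, so enrolment can no longer be enlarged but the analysis can still change. The drawback is reliance on missing at random: if loss depends on the unobserved follow-up score itself, as in the simulation, the mixed model removes only the part of the bias that pre and post scores predict. A missing-not-at-random sensitivity analysis for follow-up would address this and is optional.

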### Randomization

4.3

As organizations agreed to host the program(s) for their RW, the entire organization was randomly assigned to either the control or intervention group. This means that all participating staff from a given organization participated in the same condition. Sequentially numbered, sealed, opaque envelopes (SNOSE) with a 1:1 allocation ratio were created by a research assistant not involved in study recruitment, group allocations, training, or data collection processes. Once assigned, primary investigators were no longer blind to the group allocation.

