### Participant recruitment

4.4

Researchers recruited and sought written informed consent from participants at each initial training hosted by participating organizations. Participants had to be proficient in the English language and at least 18 years of age and employed through participating organizations as RW supporting children with I/DD in any setting (eg, family home, community, group homes) in order to participate. Ineligible staff or those who choose not to participate in the study component could still attend the training(s).

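### The seven mixed ANOVAs wait on a baseline check with no criterion and no fallback, and the pre score is never used as a covariate

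*Protocol article*

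**What the plan says.** In the protocol article, the Analyses section opens the plan for the primary and secondary outcomes with the condition "After confirming there are no baseline differences between groups", after which "seven 2 × 3 mixed analysis of variances (ANOVA) will be conducted". The seven outcomes are the knowledge score and six perception ratings. In each model the within-subjects factor is the participant's "scores on the related measure across pre, post, and" follow-up, and the between-subjects factor is the training condition. No covariate is named.

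One fallback is given: "If statistical assumptions for these analyses are not met, a more conservative approach using bootstrapping will be considered". It concerns model assumptions, not a baseline difference.

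Two design features bear on the point. Under Randomization, whole organizations are allocated, and "Once assigned, primary investigators were no longer blind to the group allocation". Under Participant recruitment, "Researchers recruited and sought written informed consent from participants at each initial training hosted by participating organizations", so individual workers enter after their organization has been allocated.

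**The concern.** The condition asks the data to establish something that a comparison of two arms of this size cannot establish. A check that finds nothing may have missed a difference large enough to matter. A check that finds something leaves the reader with no planned primary analysis, so the choice would be made after seeing the data.

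The pre score is the obvious protection against baseline imbalance and is measured for all seven outcomes. Treating it only as another outcome in the time factor makes the group comparison depend on change from pre. That contrast carries the full noise of the pre measurement, and a covariate model avoids part of it. At stake are a clearly defined primary analysis and some precision. The Type I error of the interaction test is not shown to be at risk from the check.

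**Working it through.** **Inputs from the protocol article.** 84 participants per group (168 in total), alpha 0.05, power 0.95, f = 0.125 (d = 0.25), f = 0.45 (d = 0.90), two groups and three time points.

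**Assumptions.** Correlation rho between time points of 0.3, 0.5 or 0.7; a two-sided 5% test as the baseline check; 14 workers per organization; intracluster correlation (ICC) of 0.01, 0.05 or 0.10. The article states none of these.

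**1. The plan's own sample size.** The group-by-time interaction test has noncentrality f² × N × 3/(1 − rho), with 2 and 2(N − 2) degrees of freedom.
- With rho = 0.5, f = 0.125 and N = 168, noncentrality is 0.015625 × 168 × 3/0.5 = 15.75 and power is 0.952.
- With f = 0.45 and N = 16, power is 0.970.

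Both stated sizes reproduce at rho = 0.5. For f = 0.125, rho of 0, 0.3 and 0.7 would need 332, 234 and 102. The sample-size arithmetic is not in dispute. The powers below refer to a 0.25 SD difference between arms, which is not the same quantity as f = 0.125 for the interaction, so they should not be set against the plan's 0.95.

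**2. What a passed check shows.** For a two-sample t test with 84 per arm, noncentrality is δ × √(84/2).
- δ = 0.25 SD: 0.25 × 6.48 = 1.62, power 0.36.
- δ = 0.40 SD: 0.40 × 6.48 = 2.59, power 0.73.

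Clustering is ignored here. A 0.25 SD imbalance would be missed about 64% of the time.

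**3. How often the check fails under true balance.**
- One 5% test: 5%.
- Seven independent tests, any one of which counts as failure: 1 − 0.95⁷ = 0.302. This is the upper end; correlated outcomes give less.
- A worker-level test that ignores clustering: the design effect is 1 + 13 × ICC, and the rejection rate is 2 × [1 − Φ(1.96/√design effect)].

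| ICC | Design effect | False failure per test |
|---|---|---|
| 0.01 | 1.13 | 6.5% |
| 0.05 | 1.65 | 12.7% |
| 0.10 | 2.30 | 19.6% |

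**4. Effect of the check on Type I error.** The simulation used 84 independent workers per arm, no effect and 8,000 runs per setting. Among runs that passed the check, the interaction test rejected in 4.4%, 4.7% and 4.9% at rho 0.3, 0.5 and 0.7. There is no inflation in this setting.

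**5. Precision.** With unit variance at one post-training time, the residual variance is 2(1 − rho) for change from pre and 1 − rho² with pre as a covariate. The ratio is (1 + rho)/2. Power is for a 0.25 SD effect with 84 per arm, clustering ignored.

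| rho | Change | Covariate | Ratio | Power, change | Power, covariate |
|---|---|---|---|---|---|
| 0.3 | 1.40 | 0.91 | 0.65 | 0.28 | 0.39 |
| 0.5 | 1.00 | 0.75 | 0.75 | 0.36 | 0.46 |
| 0.7 | 0.60 | 0.51 | 0.85 | 0.55 | 0.62 |

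**6. Averaging post and follow-up (rho = 0.5).** Variance is 0.75 for change and 0.50 with the covariate, giving power 0.46 and 0.62. The 2-df omnibus interaction for the same effect gives 0.37.

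**The case against.** The strongest reply is that the planned model does use the pre score. The Sample size section powers the trial "at power of 0.95 and alpha of 0.05 to detect an overall interaction effect of group by time", and that interaction cancels any constant baseline offset. It also matches the stated pre, post and follow-up hypotheses. This stands. A reader might infer that the plan leaves baseline unadjusted altogether, but the document supports only the narrower statement that pre is not a covariate.

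A reader might also infer that the check invalidates the ANOVA. The simulation does not support that. What is undefined is the branch where the check fails.

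It is tempting to quote power of 0.62 against 0.37 as the gain from adjustment. That compares a 1-df covariate analysis of the post and follow-up mean with a 2-df omnibus test. Like for like it is 0.62 against 0.46; the remaining 0.09 comes from the change of test. The gain also matters mainly near the deliberately conservative effect size: at the smallest pilot effect, d = 0.90, power at one time point with rho = 0.5 exceeds 0.999 either way.

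The article names no test, threshold or variable for the confirmation. It gives no number of enrolled organizations, only 95 potentially eligible ones. That few organizations were randomized, or that imbalance is likely, cannot therefore be asserted. Cluster randomization and recruitment after allocation make imbalance possible, and are design matters in their own right.

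Finally, an unseen analysis plan might say what follows a detected difference. That would close the missing branch, but not the reliance on confirmation or the choice of model, which the article itself states.

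**Conclusion.** The point holds in limited form. The article makes its primary and secondary analyses conditional on a confirmation that data of this size cannot give, states nothing for the case where it fails, and does not use the pre score as a covariate. The missing criterion and branch are faults whether or not the confirmation is a significance test; the error rates for the check apply only if it is one.

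The precision loss is moderate. For rho of 0.7 to 0.3, covariate adjustment saves 15% to 35% of the change-score variance, and 25% at the rho of 0.5 that reproduces the plan's own sample sizes. The absolute power figures would be lower with clustering, and the false-failure rates depend on the assumed cluster size and ICC. This is a change that should be made, but it is not evidence that the planned interaction test is biased.

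**What to change.** - Delete the baseline condition, so that the analysis runs in the same way whatever the baseline comparison shows.
- Report baseline values by arm descriptively, without p-values. Description remains useful because workers were recruited after allocation.
- For all seven outcomes, prespecify adjustment for the worker's own pre score, either as a covariate for post and follow-up or through a constrained-baseline mixed model. In both forms, account for organization. The constrained form assumes equal expected pre scores in the two arms, which recruitment after allocation could disturb; the choice should be justified. Neither form repairs selection on unmeasured characteristics.

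The cost is analysis wording only, because the pre score is already collected for every outcome. Data collection is reported as complete with analyses ongoing, so the change should be dated and should state whether outcomes by arm had been seen. The planned mixed ANOVA can be kept as a sensitivity analysis.

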### Study design and procedure

4.1

The RCT represents a multi‐center parallel two group (pain training, control training) design. Data were collected in‐person using hard copy questionnaires immediately before and after an initial training, and again at a 4‐ to 6‐week follow‐up time point using hard copy questionnaires and focus group methodology (See Figure 1 for procedure). Participating organizations were given information about the general purpose of the study as well as the training topic(s), but were not made explicitly aware of whether they were allocated to the control or intervention condition. Participants were told that the purpose of the study was to learn about the impact that training can have on RW knowledge about caring for children with I/DD. No information was provided to participants about study hypotheses.

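### Organizations are randomized, but all seven ANOVAs treat workers as independent: between-group tests are anti-conservative under any positive organization-level correlation, tests of change to the extent that organizations differ in change

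*Protocol article*

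**What the plan says.** Section 4.3 (Randomization) makes the organization the unit of allocation: "the entire organization was randomly assigned to either the control or intervention group". It adds that "all participating staff from a given organization participated in the same condition", so organizations are nested within condition.

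Section 8 (Analyses) fixes the model for pain knowledge (primary) and the six perception ratings (secondary): "seven 2 × 3 mixed analysis of variances (ANOVA) will be conducted". For all seven it names one within-subjects factor, time (pre, post, follow-up), and one between-subjects factor, condition. One-way ANOVAs and paired t tests follow as needed. If assumptions fail, bootstrapping will be considered, subject to what the software permits; the resampling unit is not stated. No organization term, cluster-robust variance or cluster-level analysis appears.

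Section 3 predicts higher knowledge and perceptions in the pain-training group than in the control group at post and at follow-up, and gains within the pain-training group. Section 5.1 caps sessions at 30 people and notes that "Training sessions were interactive in nature". Section 4.5 sizes the trial in participants: 168 in total for the group-by-time interaction.

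**The concern.** Condition was assigned to organizations, so its effect has to be judged against variation among organizations. The planned ANOVAs judge it against variation among workers, with 166 between-subject and 332 within-subject error degrees of freedom at 168 workers. Workers in one organization share an employer, and those trained together share a session and its discussion, so their scores, and plausibly their gains, will resemble each other.

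If so, standard errors are too small, and differences that arise between organizations can be declared training effects. The primary outcome and all six ratings are affected, in both the intention-to-treat and the per-protocol analysis. Because the article names the test, its factors, the follow-up tests and the fallback, this is a stated analysis in conflict with a stated design. It is not a detail left to a separate analysis plan.

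**Working it through.** **Inputs.** From the article: whole-organization allocation (4.3); a 2 × 3 mixed ANOVA (8); 168 workers, alpha 0.05, power 0.95, f = 0.125 or 0.45 (4.5). Assumed, because the article does not give them: correlation of 0.5 between a worker's repeated scores, sphericity, number and size of organizations, ICC, and the share s of organization variance that is stable over time.

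**Step 1: the article's own figures.** For the interaction, λ = f² × N × 3 / (1 − 0.5), with df 2 and 2(N − 2).
- f = 0.125, N = 168: λ = 0.015625 × 168 × 3 / 0.5 = 15.75; df 2, 332; power 0.952.
- f = 0.45, N = 16: λ = 0.2025 × 16 × 3 / 0.5 = 19.44; df 2, 28; power 0.970.

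Both totals are reproduced exactly with independent participants. The sizing therefore contains no allowance for clustering either.

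**Step 2: which correlation matters for which test.** Set the variance at each time point to 1. With a within-worker correlation of 0.5, half of it is stable and half is time-specific. Organizations contribute ICC in total, of which (1 − s) × ICC is time-specific. The ICC of change is then r = (1 − s) × ICC / 0.5 = 2(1 − s) × ICC.
- Interaction and paired t tests: design effect DE = 1 + (m − 1) × r, with m workers per organization. A fully stable organization effect (s = 1) gives r = 0 and DE = 1.
- Between-group test at one time point: DE = 1 + (m − 1) × ICC, whatever s is.

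**Step 3: actual error rate at nominal 5%.** Interaction: P(χ² on 2 df > 5.99 / DE) = exp(−2.996 / DE). Tests of a single contrast: 2[1 − Φ(1.96 / √DE)].

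Example with 12 organizations of 14 and ICC 0.05:
- s = 0.5: r = 0.05; DE = 1 + 13 × 0.05 = 1.65; exp(−1.816) = 16.3%.
- s = 0.8: r = 0.02; DE = 1 + 13 × 0.02 = 1.26; exp(−2.378) = 9.3%.
- s = 1: DE = 1; 5%.
- Between groups at post: DE = 1.65; 1.96 / √1.65 = 1.526; 12.7%.
- Paired t test: 12.7% at s = 0.5 (DE 1.65) and 8.1% at s = 0.8 (DE 1.26).

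| Organizations × workers | ICC | Interaction, s = 0.5 | s = 0.8 | s = 1 | Between groups at post |
|---|---|---|---|---|---|
| 24 × 7 | 0.02 | 6.9% | 5.7% | 5% | 6.4% |
| 12 × 14 | 0.05 | 16.3% | 9.3% | 5% | 12.7% |
| 6 × 28 | 0.10 | 44.5% | 23.7% | 5% | 30.8% |

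Simulation of the planned tests with equal clusters and no training effect agrees. The interaction rejects in about 6–7%, 9–17% and 24–46% of trials (s = 0.8 to 0.5) and in about 5% at s = 1. Between-group tests at post reject in about 6–7%, 12–13% and 31–34%.

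**The case against.** The strongest counter-argument is that a lasting difference between organizations cancels from the powered test, the group-by-time interaction, and from the paired t tests. This stands. A reader might infer that the 0.05 level certainly fails for every planned test, by a wide margin. The documents do not support that: the interaction keeps its level if organization effects are purely stable, and nothing in the article shows how much organizations differ in change. The argument does not protect between-group comparisons at a single time point, which Section 3 hypothesizes and which are inflated at any positive ICC.

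A reader might also infer that only a handful of organizations took part. The article gives no number enrolled, only a database of 95 potentially eligible organizations, and the limit of 30 is per session, not per organization. With many small organizations and a low ICC the inflation is slight, as the first row of the table shows.

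Nor is the design description false. A cluster-randomized trial can also be a "parallel two group (pain training, control training) design", and Section 4.3 discloses the allocation unit openly.

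Finally, independence is an ANOVA assumption, so the bootstrap clause could in principle reach this problem. But bootstrapping is only to be considered, and resampling workers would keep the same fault. Since the resampling unit is not stated, it cannot be said that the plan resamples workers, only that it does not commit to resampling organizations.

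**Conclusion.** The point holds: the stated analysis does not respect the stated randomization. The direction is firm for between-group comparisons under any positive organization-level correlation. For the interaction and paired t tests it depends on organizations differing in change, which group delivery makes plausible but the article does not demonstrate.

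The size cannot be computed from the documents. Under the assumptions above it runs from no inflation of the interaction test (fully stable organization effects), through modest inflation with 24 organizations at ICC 0.02, to roughly a quarter to a half of null trials declared significant with 6 organizations at ICC 0.10. If the ICC is zero, all tests keep their 5% level, but the article offers no evidence for that. The analysis should be corrected before results are reported. Section 2 says data collection is complete and analyses are ongoing, so the analysis can still be changed although the design cannot.

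**What to change.** Replace the seven mixed ANOVAs and their follow-up tests with a linear mixed model for each outcome:
- fixed effects of condition, time and condition-by-time;
- random effects of organization and organization-by-time;
- repeated measures within worker;
- Satterthwaite or Kenward-Roger degrees of freedom.

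Obtain the post and follow-up group comparisons and the within-group changes as contrasts from this model. Keep the condition main effect. Workers were recruited at the trainings, after their organization had been allocated (4.3, 4.4), and organizations knew the training topic (4.1), so equal baselines among those who consented are not guaranteed.

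If too few organizations enrolled to estimate the two organization variances, analyse baseline-adjusted organization-level means, with degrees of freedom based on the number of organizations. Any bootstrap must resample whole organizations. Report the number of organizations per arm and the observed ICC.

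The cost is revised analysis wording, some re-programming and wider confidence intervals. No new data are needed, since workers were recruited at their own organization's training and so can be linked to it.
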